#### Adverse event and serious adverse event recording and reporting

Adverse events and reactions will be defined as follows.

##### Adverse event (AE)

Any untoward medical occurrence in a patient treated on a study protocol, which does not necessarily have a causal relationship with a study intervention. An AE can therefore be any unfavourable and unintended sign, symptom or disease temporally associated with the use of the study intervention, whether or not related to that study treatment.

##### Adverse reaction (AR)

All untoward and unintended responses related to a study intervention. A causal relationship between a study intervention and an adverse event is at least a reasonable possibility, i.e. the relationship cannot be ruled out as there is evidence or arguments to suggest a causal relationship.

##### Unexpected adverse reaction (UAR)

An adverse reaction, the nature or severity of which is not consistent with the information about the trial intervention.

Serious adverse event (SAE) or serious adverse reaction (SAR) or suspected unexpected serious adverse reaction (SUSAR): Respectively any adverse event, adverse reaction or unexpected adverse reaction that:Results in deathIs life-threatening (where the term life-threatening refers to an event in which the patient is at risk of death at the time of the event; it does not refer to an event that might hypothetically cause death if it was more severe (e.g. a silent myocardial infarction))Requires inpatient hospitalisation or prolongation of existing hospitalisationResults in persistent or significant disability or incapacityConsists of a congenital anomaly or birth defectOr any other health event which in the opinion of the clinician is serious

Important adverse events that are not immediately life-threatening or do not result in death or hospitalisation but may jeopardise the subject or may require intervention to prevent one of the other outcomes listed in the definition above should also be considered serious.

As suicidal ideation and mild self-harm are a common aspect of the clinical presentation of many mood disorders, we will only rate these as adverse events if they include suicidal behaviour or the degree of self-harm puts the individual at risk of physical injury. In particular, suicidality will be deemed as an AE or SAE, if risk is categorised as level C on our risk protocol. Routine hospitalisations and planned surgery recorded at the baseline assessment visit (pre-treatment) do not require reporting as SAEs.

Any event observed by either a researcher or therapist that could be considered as SAE will be documented on the Serious Adverse Event Form and reported to the local PI. Research Assistants will be responsible for screening the AD-SUS questionnaire within 72 h of completion to check for potential serious adverse events. Identification of a potential SAE in the AD-SUS will trigger a telephone call to the participant to capture more detailed information and context of the event although this should not delay reporting. As reports on the AD-SUS are retrospective, the research team will assess any remaining risks and the local sites risk management process will be adhered to at any time to ensure participants receive support where necessary.

The local PI will evaluate the reported event for seriousness considering the available contextual information. All non-serious AE will be documented in the electronic patient record. If the issue is assessed as serious, the event must be reported to the CI, Trial Manager, local R&D department and Sponsor, immediately and no later than 24 h of being made aware of the event. Initial reports of SAE can be made via email but must be promptly followed with a detailed written report using the Serious Adverse Event Reporting Form for the Sponsor and containing sufficient detail regarding concurrent life events. The PI should ensure that follow-up information is provided when available.

The sponsor will allocate an SAE number and forward the event to the trial’s Independent Clinician who is part of the Independent Data Monitoring Committee. The Independent Clinician will rate the event to confirm or question its seriousness, with the final decision in case of discrepancy made by the PI; determine the causality of SAEs according to Table 1; and also rate SAEs with regard to its expectedness. Independent review will be conducted within 72 h and the outcome will be reported back to the local Research Assistant PI, CI, Trial Manager and sponsor by email using the SAE number allocated by the sponsor.

**Table 1 Tab1:** SAE causality rating

Relationship	Description	Event type
Unrelated	There is no evidence of any causal relationship	Unrelated SAE
Unlikely to be related	There is little evidence to suggest that there is a causal relationship (e.g. the event did not occur within a reasonable time after administration of the trial treatment). There is another reasonable explanation for the event (e.g. the participant’s clinical condition or other concomitant treatment)	Unrelated SAE
Possibly related	There is some evidence to suggest a causal relationship (e.g. because the event occurs within a reasonable time after administration of the trial treatment). However, the influence of other factors may have contributed to the event (e.g. the participant’s clinical condition or other concomitant treatment)	SAR
Probably related	There is evidence to suggest a causal relationship and the influence of other factors is unlikely	SAR
Definitely related	There is clear evidence to suggest a causal relationship and other possible contributing factors can be ruled out	SAR

SAEs classed as related and unexpected will be reported to the Research Ethics Committee by the sponsor within 7 days if it is deemed to be life-threatening or results in death and 15 days if it is non-fatal and non-life threatening (see Fig. 3).

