### Data management {19}

Randomisation, data management and quality assurance will be undertaken by ExeCTU under the supervision of the CI, senior trial statistician and quality assurance manager. Routine clinical notes will be stored according to standard practice within the NHS services hosting the research. Recordings of the videoconferencing therapy sessions along with the automatically produced transcripts of the sessions will be stored on a secure server at the University of Surrey where they will be accessible to the lead scientists for purposes of therapist supervision and manual adherence checks. Data from the assessments will be entered by the research team on a secure, web-based system maintained by the ExeCTU. Data from online questionnaires will be quality checked by the research team. Consent forms will be stored separately from data and data will be anonymised wherever possible.

The datasets generated during and/or analysed during the trial will be stored in a non-publicly available repository at Sussex Partnership NHS Foundation Trust upon publication of main study results. Anonymised data may be accessed and analysed by members of the project team and by researchers collaborating with members of the project team on the analysis of these data. All personal identifiable data, with the exception of the consent form and the video recordings, will be destroyed as soon as the study closes, unless participants have consented to be contacted for future research, in which case we will keep their contact details for 5 years. Audio recordings of qualitative interviews will be destroyed immediately after transcription. Research data with personal information removed and replaced through a code and original research records, including video recordings of assessment interviews and therapy sessions, will be retained for 10 years, before being destroyed. The electronic records will be kept for 10 years after the end of the study. Publications will not contain any patient-identifiable information.

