### Confidentiality {27}

Any information collected as part of the trial will be kept strictly confidential within the research team and the services involved. Both within the research team and the services confidentiality will be broken only in exceptional circumstances, if it is felt by the researcher or therapist that a patient or someone else is at immediate risk and the team will need to contact GPs or other relevant professionals.

All data will be stored and processed in line with General Data Protection Regulation (GDPR, 2018). Personal data will be link-anonymised and identified by a code known only to the research team. Names and contact details will be stored in password-protected files on secure servers and separately to link-anonymised data. In order to assess manual adherence and therapist competency, therapy sessions will be video recorded with the consent of all participants appearing in the recording. Access to these recordings and the transcripts of the sessions will be restricted to the research team and collaborating researchers. Recordings and anonymised transcripts will be stored on secure servers at the University of Surrey.

Direct quotations from qualitative interviews may be used; however, it will not be possible to identify the participant from these. Clinical records will be stored on secure servers with access restricted to the trial manager and clinical team.

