### Composition of the data monitoring committee, its role and reporting structure {21a}

We have set up an Independent Data Monitoring Committee (IDMC) comprising a chair ([name], University of York), an independent mental health statistician and a clinician. The IDMC will review serious adverse events that are thought to be trial- or treatment-related and look at outcome data regularly during data collection. As the TSC, the IDMC is independent from the sponsor and has no competing interests. The TSC and IDMC will meet on a half-yearly basis.

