### Adverse event reporting and harms {22}

#### Risk monitoring

In order to identify risk issues, research assistants will screen questionnaires within 72 h of completion to check for increases in suicidality and any service use that may be indicative of a serious adverse event. A score of more than 0 on the PHQ-9 item 9 (that represents a change from the previous trial assessment) and reports of suicidal ideation, intent, plans or urges, and any risk of harm to self or others in the MINI interview or other contexts will be deemed as risk issues. Identification of a risk issue will trigger the trial team to capture more detailed information and context to assess risk in line with the trial risk protocol. Where necessary participants will be provided with support in line with the local sites’ risk management process.

In the MBCT arm, the site RA will routinely monitor PHQ-9 scores on a weekly basis prior to each session (or as soon after as possible in the event of participant non-completion) and immediately email the mindfulness teacher and PI if:A participant’s score has increased by 6 points or more from baseline assessment, specifying the amount of increase, and/orA participant scores 1 or more on item 9 of PHQ-9, specifying what the score is and whether this score is typical or represents a change

The mindfulness teacher or appropriate clinical delegate will follow the study risk protocol to ensure appropriate contact is made with the participant to discuss their mental state, current risk and what is needed to keep themselves safe. Information from this conversation will be considered by the therapist and PI to answer the question of whether a participant should continue with treatment. All instances in which the risk protocol has been enacted will be documented using the Risk Assessment Form and logged in the study risk management log together with contextual information and their classification.

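### Non-serious adverse events are directed to the electronic patient record, with no stated route to a structured trial record from which they could be summarised by arm

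*Protocol article*

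**What the plan says.** The article defines adverse events and adverse reactions without regard to seriousness. An adverse reaction, for example, covers "All untoward and unintended responses related to a study intervention". The local PI then judges each reported event for seriousness, and from there two routes are described.

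- **Serious events** are reported within 24 hours to the chief investigator, trial manager, R&D department and sponsor. They receive an SAE number and are rated by an independent clinician for seriousness, causality (Table 1) and expectedness.
- **Non-serious events** get one sentence: "All non-serious AE will be documented in the electronic patient record".

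On where records are kept and who sees them:

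- Data management {19}: "Routine clinical notes will be stored according to standard practice within the NHS services hosting the research". Of the trial system it says: "Data from the assessments will be entered by the research team on a secure, web-based system maintained by the ExeCTU".
- Confidentiality {27}: "Clinical records will be stored on secure servers with access restricted to the trial manager and clinical team".
- Data monitoring committee {21a}: "The IDMC will review serious adverse events that are thought to be trial- or treatment-related and look at outcome data regularly during data collection".

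Two other records are kept by the trial. Under the adverse event definitions: "Any event observed by either a researcher or therapist that could be considered as SAE will be documented on the Serious Adverse Event Form". Under Risk monitoring, each use of the risk protocol is "documented using the Risk Assessment Form and logged in the study risk management log".

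**The concern.** The adverse event section is specific about serious events, down to hours, forms and identifiers, and then names a different destination for everything else. This is a stated recording rule, not detail left for another document. An analysis plan can tabulate only what was collected in usable form. If non-serious events sit as entries in patient records, a table by arm depends on someone going back to find and code them.

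The trial is meant to support a decision on adopting MBCT for non-responders within IAPT. A short list of harms would be hard to interpret if it might reflect where events were filed. A difference between arms would be hard to interpret if one arm was watched more closely than the other.

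**Working it through.** The point rests on no power, effect size or rate, so the check is a comparison of the relevant sections.

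**1. Destination.** Adverse event reporting and harms {22} names the electronic patient record for non-serious events. It mentions no trial form, database field or transfer step for them.

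**2. Access.** Confidentiality {27} restricts clinical records to the trial manager and clinical team. This applies only if the electronic patient record is one of those clinical records. That is the likely reading, but it is not stated.

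**3. Trial database.** Data management {19} describes assessment data as entered on the ExeCTU system. It does not mention adverse events, and it does not exclude them.

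**4. Oversight.** The IDMC's stated remit is related serious events and outcome data. Non-serious events are not named.

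**5. How much the other trial records cover.**

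| Record | What enters it | What it leaves out |
|---|---|---|
| Serious Adverse Event Form | Events that might be serious, before the PI's judgement | Events never thought possibly serious. For an event the PI then judges non-serious, the only onward step described is the patient record |
| Risk Assessment Form and risk log | Risk issues: suicidality, harm to self or others, PHQ-9 rises | Adverse events of other kinds. It also holds entries that are not adverse events, since suicidal ideation counts as one only under stated conditions |
| PHQ-9 and GAD-7 deterioration (secondary outcomes) | Symptom-score worsening in both arms | Events as such |

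Each record captures part of the class, and together they do not capture all of it. Table 1 rates causality for serious events only, so a non-serious adverse reaction is defined but no described step identifies it as one.

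**6. Detection by arm.** Both arms have scheduled questionnaires at 10 and 34 weeks, screened by research assistants within 72 hours. For the MBCT arm, Risk monitoring adds a PHQ-9 check before each weekly session, with alerts to the teacher and PI. The course has eight sessions. At one check per session, the described occasions are 8 + 2 = 10 in MBCT and 2 in TAU, leaving aside the one interview each arm has. The count is indicative only. These checks look for risk issues, not all adverse events, and Secondary outcomes mentions weekly symptom tracking without naming an arm. The alert procedure itself is described for MBCT only.

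**7. Scale.** The rule applies to all 2 × 117 = 234 participants. The article gives no rate of non-serious events, so no count of affected events follows.

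**The case against.** A reader might infer something stronger: that the patient record is the sole place these events are kept, that statisticians and the IDMC are shut out of it, and that the trial therefore cannot report non-serious harms by arm. The article does not support this.

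- It does not say that the patient record replaces a trial record.
- Events that might be serious go on a trial form before seriousness is judged, and risk events go in a study log.
- The trial manager belongs to the core research team and is expressly given access to clinical records, so events could be extracted and linked to allocation. Statisticians and monitoring committees usually work from extracts, so their absence from an access list prevents nothing.
- Serious events are not the sole harms information. Deterioration on PHQ-9 and GAD-7 is reported, service use is collected, and interviews in the MBCT arm explore unanticipated effects.

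It can also be said that this is a condensed article. Case-report forms and tabulation may sit in the full protocol or the SAP, neither of which is shown, and the sections compared above do not contradict one another. The abbreviation list includes a Negative Effects Questionnaire that does not appear among the described measures. With the schedule figure not shown, that counts neither way.

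These arguments rule out the stronger reading. They leave standing that the article chooses a destination for non-serious events, that the other records cover only part of them, and that it states no route from the patient record to the trial data.

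**Conclusion.** The point holds in limited form. Under the stated rule, non-serious adverse events as a class have no structured trial record, and the described surveillance is closer in the MBCT arm. Harms data by arm would be poorer than they need be. Reporting them is not impossible, and nothing here shows that events would be lost.

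The size cannot be put as a number of events, for want of a rate. In scope it covers every non-serious event among the 234 participants that does not also reach the SAE Form or the risk log.

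The conclusion rests on two readings: that the electronic patient record is among the restricted clinical records, and that the full protocol does not already provide a trial log for these events. If it does, one sentence in the article saying so would settle the matter.

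**What to change.** Amend the sentence on non-serious events so that each one already being documented is also logged on the existing ExeCTU system, with:

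- date;
- brief description;
- how it was found: scheduled assessment (both arms), or therapist or weekly-monitoring contact.

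In the IDMC reports and final results, tabulate events and participants with events descriptively by randomised arm and by source. The source column lets a reader compare the arms on events found at the common assessments, apart from those found through MBCT contact.

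The cost is a short extra form for staff who already record the event, one descriptive table, and a modest addition to what the IDMC receives. No new assessment is needed, nor formal causality adjudication of non-serious events. The change concerns data recording and leaves clinical management and the risk protocol as they are.

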**Fig. 3 Fig3:**
[figure not shown]
SAE reporting flowchart

The PIs will take responsibility for making sure that the local risk management procedures are adhered to at all times and that all risk issues are followed up until resolution.

### Frequency and plans for auditing trial conduct {23}

The research will be audited through established procedures at the sponsor’s R&D department.

### Plans for communicating important protocol amendments to relevant parties (e.g. trial participants, ethical committees) {25}

In case amendments to the protocol are needed, we will seek to obtain sponsor approval for the amendment to be submitted. We will prepare a submission to the REC through the IRAS system (https://www.myresearchproject.org.uk/help/hlpamendments.aspx#Amendment-Tool), authorised by the CI and the sponsor. The CI will communicate the outcome of the review process and any resulting changes of the protocol to the sites and inform participating organisations. Trial registrations and the published protocol will be amended accordingly.

## Dissemination plans {31a}

The trial data may have the potential to inform changes in current practice within IAPT. The evaluated treatment manual of MBCT for patients with current symptoms of depression will facilitate training and dissemination of the approach within IAPT and other contexts. Insights from qualitative analyses will provide information on implementability. The findings of the research will be disseminated using the widest range possible of peer-reviewed scientific journals and professional publications. We will present results at conferences and workshops and disseminate findings through media and social media where possible. We will also disseminate findings on a local level, to participants, services and other stakeholders.

## Discussion

This trial will provide definitive evidence on whether the use of MBCT in depressed IAPT high-intensity treatment non-responders is clinically effective and cost-effective. The evidence from this trial is intended to inform changes in current practice within IAPT. Should MBCT for IAPT treatment non-responders prove clinically effective and cost-effective, the data from this study together with accumulated evidence from previous research on MBCT for depressed treatment non-responders would justify changes in service provision that will have significant impact on the mental and physical health of the large number of patients who have come to the end of the IAPT pathway but have not recovered sufficiently.

## Trial status

The project started on the 1st of January 2021 and sites have been initiated for recruitment in April and May 2021 (Exeter: 20/04/2021; Sussex and London: 26/04/2021). The study database was signed off on 18/05/2021 and first consents were obtained on 9/06/2021 in Exeter, 22/05/2021 in London and 01/07/2021 in Sussex. We expect recruitment to be completed in the middle of October 2022. Should targets for the current cohorts not be reached, recruitment will remain open into the first quarter of 2023.

## Data Availability

The CI will serve as the custodian of the trial data. There are no contractual agreements in place that would limit access for the investigators.

## Abbreviations

AD-SUS: Adult Service Use Schedule
AE: Adverse event
AR: Adverse reaction
CI: Chief investigator
CTQ: Childhood Trauma Questionnaire
CTU: Clinical Trials Unit
DMEC: Data Monitoring and Ethics Committee
DSM-5: Diagnostic and Statistical Manual of Mental Disorders, Fifth Edition
EQ: Experiences Questionnaire
EQ-5D: EuroQoL 5-Dimension instrument
FFMQ: Five Factor Mindfulness Questionnaire
GAD-7: Generalized Anxiety Disorders Questionnaire-7
GP: General Practitioner
HRA: Health Research Authority
IAPT: Increasing Access to Psychological Therapies
ICC: Intra-class correlation
IRAS: Integrated Research Application System
ISRCTN: International Standard Randomised Controlled Trial Number
MCID: Minimal clinically important difference
MBCT: Mindfulness-Based Cognitive Therapy
MBI-TAC: Mindfulness-Based Interventions – Teaching Assessment Criteria
NEQ: Negative Effects Questionnaire
NHS: National Health Service
NICE: National Institute for Clinical Excellence
NIHR: National Institute for Health Research
PHQ-9: Patient Health Questionnaire 9
PIS: Patient information sheet
QALY: Quality-adjusted life year
RCT: Randomised controlled trial
RfPB: Research for Patient Benefit
SAE: Serious adverse event
SAR: Serious adverse reaction
SCID: Structured Clinical Interview for DSM-5
SUSAR: Suspected unexpected serious adverse reaction
TAU: Treatment as usual
TSC: Trial Steering Committee
UAR: Unexpected adverse reaction
UK: United Kingdom
WEMWEBS: Warwick-Edinburgh Mental Wellbeing Scale (WEMWBS)
